### Intervention

#### Preparation Program for Midwives

Before the commencing of the study, a preparation program will be provided to the recruited 6 midwives. The program was developed and informed by the research team’s midwifery experience, engagement with the literature and a systematic review [8].

The aim of the midwifery preparation program is to provide midwives with comprehensive and evidence-based practice information on the management of pushing in particular the management of spontaneous pushing during the second stage of labor. This will ensure that midwives feel confident to support women with spontaneous pushing during the second stage of labor. The program will run over 3 weeks and will include 6 sessions, and 5 hours in total over 3 weeks. The training plan is displayed in Table 4.

**Table 4 table4:** Preparation program for midwives.

Week and session		Topic	Details	Duration (min)
**Week 1**				
	Session 1	Induction	Introduction of the project and the research team Midwives to introduce themselves and discuss their expectations of the program, allowing the researcher to answer any questions they may have The procedure of the feasibility study The role of the midwife in the feasibility study Time for question and answers	50
	Session 2	Review of the current evidence	Pushing during the second stage of labor: a scoping review Directed pushing vs spontaneous pushing: meta-analysis Discussion	40
**Week 2**				
	Session 3	How to support spontaneous pushing	Standard procedures of directed pushing management Strategies to support spontaneous pushing Comparison of spontaneous pushing and directed pushing Simulation in pairs Time for question and answers	90
	Session 4	Q&A: Expectations or questions on pushing management	This session will be conducted digitally using the social media app Tencent meeting In this session, midwives will be encouraged to share their expectations or questions on managing the second stage of labor Questions about the process of the study will be answered by the researcher	30
**Week 3**				
	Session 5	Further discussion of the research and participant withdrawal options	A brief recap of the research and refresh of the training content (highlight the items that directly relate to midwives) Safety and distress protocol will be explained to midwives Withdrawal options and their procedures will be explained to midwives	30
	Session 6	Scenario-based learning and practice	Scenario-based learning Time for question and answers	50 minutes

#### Strategies to Support Spontaneous Pushing During Labor

Spontaneous pushing encourages a woman to push following her bodily instincts. A standardized step-by-step procedure may not be suitable for every laboring woman. The following strategies are shown to facilitate the spontaneous pushing during labor: (1) encourage woman to select the most comfortable position for her during pushing [7]; (2) offer information about progress of her labor and about any sensations she may feel [25]; (3) affirm to the woman how well her body is working and encourage her to work with and listen to her body urges [25]; (4) support the woman to wait for pushing urges, instead of coaching her to push immediately when the contraction begins [25]; (5) support the woman to push with open glottis, including sighing, moaning, or even crying [26]; and support and encourage the woman to give several short pushes (usually 4 to 6 s) instead of 1 long push (8 to 10 s or even longer) [27].

### Outcomes

#### Overview

The outcomes measured will include 3 domains: feasibility, acceptability, and effectiveness.

#### Primary Outcomes

The primary outcomes will include (1) feasibility (recruitment rates, retention rates, and attendance rates of participants) and (2) acceptability (women’s and midwives’ perspectives and acceptability of the intervention).

#### Secondary Outcomes

Secondary outcomes will include the duration of the second stage of labor, maternal pushing position, mode of birth, rates of cesarean birth, perineal laceration, the rates of episiotomy, newborn Apgar scores, rates of newborn resuscitation, and rates of transfer to the neonatal intensive care unit. Table 5 illustrates the primary and secondary objectives, outcomes, criteria for success, methods for analysis, and measurement tools.

**Table 5 table5:** Primary and secondary outcome criteria, analysis, and measurement.

Objectives, outcomes, and criteria for success				Methods of analysis		Measurement or tool
**Primary objectives: To test the feasibility of a future RCT^a^ to compare the effects of spontaneous pushing and directed pushing for maternal and neonatal outcomes**						
	**Recruitment**					
		Complete recruitment within 6 months	Descriptive		Researcher work log	
		Women recruited/women accessed×100% > 10%	Descriptive		Researcher work log	
		Number of women recruited/number of women who bring Information Sheet home×100% > 30%	Descriptive		Researcher work log	

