### Objectives

The primary objective is to test the feasibility of a future RCT to compare the effects of spontaneous pushing and directed pushing for maternal and neonatal outcomes. The secondary objective is to explore the effectiveness of spontaneous pushing and directed pushing for women without an epidural during the second stage of labor.

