## Methods

### Study Design

This feasibility study is a nonrandomized, single-group, noninferiority trial. All participants will receive the intervention (spontaneous pushing). A mixed methods approach will be used to assess the primary and secondary outcomes. This protocol adheres to the SPIRIT (Standard Protocol Items: Recommendations for Intervention Trials) guidelines (Multimedia Appendix 1) [21].

Table 1 illustrates the objectives, outcomes, and the corresponding study design. Tables 2 and 3 illustrate the chart of the study designs, visits, and assessments for both women and midwives. The flow diagram (Multimedia Appendix 2) demonstrates the enrollment, allocation, follow-up, and assessment process for women to compare the effectiveness of the intervention.

**Table 1 table1:** Objectives, outcomes, and study design.

Objectives and outcomes		Study design
**Primary objective: To test the feasibility of a future RCT^a^ to compare the effects of spontaneous pushing and directed pushing for maternal and neonatal outcomes**		
	Feasibility: recruitment rates, retention rates, and attendance rates of participants	Quantitative study design
	Acceptability: women’s and midwives’ perspectives and acceptability of the intervention	Quantitative study design (survey for women) and qualitative design (interviews for midwives)
**Secondary objective: To explore the effectiveness of spontaneous pushing and directed pushing for women without an epidural during the second stage of labor**		
	Maternal and neonatal outcomes	Quantitative study design

^a^RCT: randomized controlled trial.

**Table 2 table2:** Chart of the study design, visits, and assessment for women.

Time point			Visit 1: during late pregnancy at clinics		Visit 2: at clinics or admission to the prenatal ward		Visit 3: during the second stage of labor		Visit 4: within 2 hours after birth		Visit 5: during the stay in the postnatal ward

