### Participants

All participants will be recruited from the Fourth Hospital of Shijiazhuang, Hebei Province, China. In total, 105 women will be recruited to receive the intervention. At the same time, 105 sets of medical notes will be identified, and relevant information will be extracted to compare health outcomes between the 2 cohorts. These medical notes will be from women who received standard care, that is, “directed pushing” during the second stage and met the same selection criteria as the women in the spontaneous pushing group. The women whose notes will be reviewed will not be recruited into this study, but permission has been obtained from the site-specific hospital to examine the deidentified medical notes. The demographic data, that is, age and the parity and labor care section of the medical notes will be reviewed and examined and parity in 2 cohorts will be matched for further comparison.

Six midwives will be recruited to support spontaneous pushing. They will be rostered to cover all 4 shifts of the roster to ensure that every recruited woman will be supported to push spontaneously by a recruited and trained midwife. All recruited midwives will be interviewed for the qualitative study part.

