## Results

This study will provide both quantitative and qualitative data on the feasibility of a future RCT, including the rate of and ease of recruitment, retention, and attendance of participants during the process. Qualitative results from midwives’ focus group interviews will be presented to illustrate midwives’ acceptability of the intervention. In addition, a series of labor and birth outcomes will be compared to explore the effectiveness of the intervention.

Data collection took place between May and October 2023. A total of 110 women were invited to participate in the intervention of spontaneous pushing. Midwives’ interviews were conducted and will be transcribed for analysis in March 2024. The study is expected to conclude in May 2024.

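### The Table 5 recruitment criteria measure consent to a study in which every woman receives spontaneous pushing, so meeting them leaves acceptance of random allocation, part of the primary objective, untested

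*Protocol article*

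**What the plan says.** The Objectives section states: "The primary objective is to test the feasibility of a future RCT to compare the effects of spontaneous pushing and directed pushing". Study Design describes the study this way: "This feasibility study is a nonrandomized, single-group, noninferiority trial". It adds: "All participants will receive the intervention (spontaneous pushing"). The directed-pushing comparison uses 105 sets of medical notes, and Participants says of that cohort: "The women whose notes will be reviewed will not be recruited into this study".

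Table 5 places three recruitment criteria for success under the objective of testing RCT feasibility:

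- "Complete recruitment within 6 months"
- "Women recruited/women accessed×100% > 10" (per cent)
- "Number of women recruited/number of women who bring Information Sheet home×100% > 30" (per cent)

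Results returns to the same purpose: "This study will provide both quantitative and qualitative data on the feasibility of a future RCT, including the rate of and ease of recruitment". Strengths and Limitations names two limitations, mixed parity and midwives using spontaneous pushing with routine-care women. It does not say that consent to randomization goes untested.

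**The concern.** A woman who joins this study knows which way of pushing she will be supported to use. A woman who joins a randomized trial must accept that chance decides, and that she may be allocated to directed pushing. These are different decisions, and the rate of the first need not equal the rate of the second.

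The study can meet every criterion in Table 5 without learning how women respond to the second decision. If the conclusions then report RCT feasibility without qualification, a single-arm consent rate would be carried into the planning of a randomized trial as though it had been measured under randomization.

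**Working it through.** The plan has no computed figure to reproduce on this point. The thresholds are set values, and the sample size of 105 per group plays no part. The check sets each Table 5 criterion for the primary objective against what a randomized trial would need.

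| Table 5 criterion | What it is measured on | Bears on acceptance of random allocation? |
|---|---|---|
| Recruitment done in 6 months | Women consenting to certain spontaneous pushing | No |
| Recruited / accessed above 10% | Same consent, all women accessed | No |
| Recruited / took sheet home above 30% | Same consent, women who took the sheet | No |
| Loss to follow-up below 30% | Study participants, all in one arm | No |
| Completed spontaneous pushing / recruited above 30% | Recruited women, with no directed-pushing counterpart | No |
| Questionnaire returned / completed spontaneous pushing above 80% | Women who have had the intervention | No |
| Midwives completing all training sessions above 80% | Midwives | No |
| Survey score above 4 of 5 (childbirth experience scale above 3 of 4) | Women surveyed, about the intervention | No |
| Midwives' focus group | Midwives, no threshold stated | Not stated |

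No row conditions on allocation by chance, and none concerns a woman accepting directed pushing within a trial.

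The quantities can be written as follows.

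- p1 = the share of accessed women who consent when spontaneous pushing is certain. The study measures this.
- p2 = the share who would consent when allocation is random. The future trial needs this.
- r = p2 / p1, so p2 = r × p1. The article gives no information on r.

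The next figures only illustrate how far the 10% criterion depends on r. Both the values of p1 and those of r are assumptions. Take p1 = 11%, which just passes.

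- r = 1: p2 = 11% × 1 = 11.0%
- r = 0.75: p2 = 11% × 0.75 = 8.3%
- r = 0.50: p2 = 11% × 0.50 = 5.5%
- r = 0.25: p2 = 11% × 0.25 = 2.8%

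For p2 to stay above 10%, r must exceed 0.10 / p1:

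- p1 = 11%: 0.10 / 0.11 = 0.91
- p1 = 20%: 0.10 / 0.20 = 0.50
- p1 = 30%: 0.10 / 0.30 = 0.33

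Nothing in the article confines r to values below 1. With p1 = 9%, a fail, and r = 1.25, p2 = 9% × 1.25 = 11.25%, a pass. So neither a narrow pass nor a narrow fail shows on which side of 10% a randomized trial would fall. A p1 far above the threshold gives more room, but still no estimate of p2.

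**The case against.** The strongest reply is that this is a disclosed and reasoned design. The article calls itself nonrandomized and single-group, and under Aims it explains that a change of practice calls for a feasibility step first and that doctoral time is limited. Checking that the new arm can be delivered is a legitimate first stage. Access to women, loss to epidural use (around 65% of primiparous women at the hospital), completion of pushing, questionnaire return and midwife training all bear on whether a trial could run. This stands. The fault lies in what may be concluded from the recruitment rates, not in choosing a single arm.

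The second reply is that the women's survey has open-ended questions and covers the experience of joining the study, and that the article ties the survey and interviews to procedure, enablers and barriers. Neither instrument is shown, so it cannot be said that randomization is never raised. This also stands in part. But no stated criterion depends on such answers, and the women surveyed were never offered randomization. On midwives, the limitations already name crossover into routine care, although no Table 5 criterion measures it.

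Three stronger readings are tempting, and the article does not support them.

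- **That the plan treats passing the recruitment thresholds as proof of RCT feasibility.** They stand beside retention, attendance and acceptability criteria, and Data Analysis says that quantitative and qualitative findings will be combined.
- **That the single-arm rate is an upper bound for a trial.** Directed pushing is the hospital's default, so some women who decline certain spontaneous pushing might accept a chance of usual care.
- **That the number of extra women to approach can be calculated.** This needs a trial sample size and an acceptance rate. The article gives neither, and it says that this study is meant to inform the sample size.

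**Conclusion.** The point holds as a mismatch between objective and measurement. The recruitment criteria are success criteria for the feasibility of a randomized trial, but they measure consent to a study with one known allocation. Every stated criterion could be met with acceptance of random allocation, and of allocation to directed pushing, left untested. The limitations do not say so.

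The consequence has no derivable size. The ratios in the check rest on assumed values and show only that a rate near 10% does not settle the matter. The trial's rate is likely lower than the single-arm rate, but that is a judgement and the direction is not established.

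The conclusion uses only the article's own statements of objective, design, comparator and criteria. These are set out explicitly, so the point does not depend on detail left to a fuller protocol or an analysis plan.

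**What to change.** **Wording, possible at any stage.** In Table 5, in Strengths and Limitations and in Conclusions, state that the recruitment rates come from a nonrandomized single-arm study, do not measure willingness to be randomized, and may differ from the rate in a randomized trial (likely lower, direction not established). Limit the feasibility conclusion to recruiting for and delivering spontaneous pushing.

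**Data, where they can still be collected.** Add one question on whether the woman would have joined if chance had decided how she was supported to push. It is best put to all women approached, including those who decline. Table 5 counts questionnaires among women who completed spontaneous pushing, after exclusions for epidural use and cesarean birth, so answers from that group alone should not be applied to everyone approached. Add one focus group prompt on whether midwives could keep to the allocated arm.

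**If collection has closed.** Results reports that data collection ran from May to October 2023 and that the interviews were done, with transcription due in March 2024. In that case, review the transcripts and the open-ended survey responses for views on allocation, report what is found, and state plainly if the topic did not arise. The question and the prompt then pass to the next study.

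**Cost.** The wording costs almost nothing. The question and the prompt need no extra visit for recruited women, and a brief contact with decliners at the time of approach. The drawbacks are that stated willingness is hypothetical and that the feasibility claim becomes narrower.

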	**Retention**					
		Loss of follow-up under 30%	Descriptive		Researcher work log	
		Number of women who completed spontaneous pushing during labor/number of women recruited×100% > 30%	Descriptive		Researcher work log	
		Number of women who completed the postnatal questionnaire/number of women who completed spontaneous pushing during labor×100% > 80%	Descriptive		Researcher work log	
	**Attendance of participant**					
		Percentage of completion of all sessions of midwives’ preparation program (midwives) > 80%	Descriptive		Researcher work log	
	**Acceptability of the “intervention”**					
		Overall score of the questionnaire survey above 4 out of 5 (Childbirth Experience Questionnaire above 3 out of 4)	Descriptive		Questionnaire survey	
		Midwives’ focus group	Framework analysis method		Qualitative data	
**Secondary objectives: To explore the effectiveness of spontaneous pushing and directed pushing for women without an epidural during the second stage of labor**						
	**Duration of the second stage of labor**					
		From full cervical dilation to the birth of the baby	Mean (SD) or medians for continuous variables		Case report forms	
	**Mode of birth**					
		Normal vaginal birth, forceps extraction, vacuum extraction, breech delivery, and cesarean birth	n (%) for categorical variables		Case report forms	
	**Perineal laceration**					
		Intact, I degree, II degree, III degree, and IV degree	n (%) for categorical variables		Case report forms	

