### Sample Size Determination

One of the objectives of the feasibility study is to gain estimates for a sample size calculation in a future RCT [22]. Although a formal sample size calculation is not necessarily needed in a feasibility study, the sample size was calculated based on the duration of the second stage of labor as a parameter outcome in previous studies. Statistical power analysis was used to estimate sample size in PASS (version 15.0; NCSS LLC, USA) software with statistical power at 90%, α at .05, and dropout rate at 20%. The sample size was calculated to be 105 in each group. Based on clinical judgment and the number of laboring women eligible in the site-specific hospital, a sample size of 105 is set for each group.

To cover all 4 shifts of the roster, a total of 6 midwives will be recruited to deliver the intervention. All the midwives recruited to the study will be interviewed at the end of the study to assess midwives’ acceptability and experience participating in the study.

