	**Episiotomy**					
		Mediolateral episiotomy, midline episiotomy, and intradermal suture	Mean (SD) or medians for continuous variables		Case report forms	

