### Data Analysis

The data in this study include both quantitative and qualitative data. For quantitative data, “intention-to-treat” analysis will be used. Statistical description will be conducted by the description of mean value, SD, number of cases, and percentage. Pearson chi-square test will be conducted for categorical variables. Independent group 2-tailed *t* test will be conducted for continuous variables. The threshold for statistical significance will be set at .05. For qualitative data, a framework method will be used, which is commonly applied for the thematic analysis of interview transcripts [30]. After a verbatim transcription of the audio recording, the framework method will help to create and apply an analytic framework in the data analysis process in 5 steps (data familiarization, framework identification, indexing, charting, mapping, and interpretation) [31]. The quantitative and qualitative data will be combined in order to compile recommendations from the feasibility in order to conduct a future RCT.

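### Table 5 leaves open whether a woman with an unextended episiotomy counts as Intact or as torn, so the laceration comparison depends on coding; a suture technique is also listed as an episiotomy level

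*Protocol article*

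**What the plan says.** The Secondary Outcomes section of the protocol article names the two perineal outcomes side by side: "perineal laceration, the rates of episiotomy, newborn Apgar scores". Episiotomy is therefore meant as a rate.

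Table 5 gives each its own row:

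- **Perineal laceration:** levels "Intact, I degree, II degree, III degree, and IV degree", summarised as "n (%) for categorical variables".
- **Episiotomy:** levels "Mediolateral episiotomy, midline episiotomy, and intradermal suture", summarised as "Mean (SD) or medians for continuous variables".

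The Data Analysis section adds that "Pearson chi-square test will be conducted for categorical variables" and that "The threshold for statistical significance will be set at .05". The article does not say where an episiotomy falls on the laceration scale. The outcomes are extracted from medical notes onto a self-designed case report form (CRF), which is not shown.

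**The concern.** An episiotomy and a spontaneous tear are competing ways for the perineum to be injured. A woman who is cut without extension has no spontaneous tear, so one coder may enter Intact. Her perineum is nevertheless incised, so another may enter II degree. The printed levels allow both. If one cohort has more episiotomies, the laceration comparison partly measures how often women were cut, and the coder's choice decides which cohort that favours.

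The episiotomy row has its own fault. Mediolateral and midline are types of incision, whereas intradermal suture is a way of closing skin. It can accompany either incision or follow a spontaneous tear. The three levels are therefore not mutually exclusive, and a sutured tear could enter the numerator of the episiotomy rate. A mean or median also does not suit an item that the outcome list calls a rate.

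At stake is the direction of a reported maternal outcome in a comparison of two non-randomised cohorts. The researcher who recruits the women also extracts the outcomes (Recruitment of Women; Case Report Form), so an open coding choice would be made with the cohort known.

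**Working it through.** **The plan's own figures.** The article states no rate for laceration or episiotomy, so there is no perineal figure to reproduce. The only design figure is 105 per group. It rests on second-stage duration, and without a stated difference, SD or margin it cannot be recomputed. It serves here only as the denominator, assuming that all 105 women per cohort contribute.

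**Notation.** Let *e* be the episiotomy rate and *i* the proportion with no tear among uncut women, with subscripts S (spontaneous) and D (directed). All episiotomies are taken as unextended.

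- Coding A (cut counts as Intact): P(Intact) = *e* + (1 − *e*)*i*
- Coding B (cut counts as not intact, for example II degree): P(Intact) = (1 − *e*)*i*

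Within a cohort the two codings differ by exactly *e*. The between-cohort difference (S minus D) under A therefore equals the difference under B plus (*e*S − *e*D). Changing the coding moves the result by the full episiotomy gap, whatever the tear rates are.

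If *i* is the same in both cohorts:

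- Difference under A = −(*e*D − *e*S)(1 − *i*)
- Difference under B = +(*e*D − *e*S)*i*

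These have opposite signs whenever *e*D differs from *e*S and *i* lies strictly between 0 and 1.

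**Illustration 1 (assumed: *e*D = 0.40, *e*S = 0.15, *i* = 0.40 in both).**

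- A: directed 0.40 + 0.60 × 0.40 = 0.64; spontaneous 0.15 + 0.85 × 0.40 = 0.49. Difference −15 points. Pearson chi-square without continuity correction on 67/105 vs 51/105: p = 0.026.
- B: directed 0.60 × 0.40 = 0.24; spontaneous 0.85 × 0.40 = 0.34. Difference +10 points. 25/105 vs 36/105: p = 0.09.
- Check: −15 − 10 = −25 points, which equals 15% − 40%.

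**Illustration 2, smaller gap (assumed: *e*D = 0.30, *e*S = 0.20, *i* = 0.40 in both).**

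- A: 58% directed vs 52% spontaneous, 61/105 vs 55/105, p = 0.41.
- B: 28% vs 32%, 29/105 vs 34/105, p = 0.45.
- The sign changes, but neither result is distinguishable from chance.

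**Illustration 3, rare episiotomy (assumed: *e*D = 0.10, *e*S = 0.05).**

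- With *i* = 0.20 in both: A gives 29/105 directed vs 25/105 spontaneous (−3.8 points, p = 0.53); B gives 19/105 vs 20/105 (+1.0 point, p = 0.86).
- With *i* = 0.20 directed and 0.30 spontaneous: A gives +5.7 points and B gives +10.5 points, so there is no reversal.

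**Wider grid (assumed).** *e*D ran from 10% to 60%, *e*S from 5% to below *e*D, and *i* from 10% to 50%. With equal *i*, the sign differed between codings in all 330 scenarios, as the algebra requires. With *i* free to differ between cohorts, it differed in 809 of 1,650 (49%). These counts describe the grid and are not a probability for this study.

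**The case against.** Most of the opposing case concerns how far the point reaches, and much of it stands.

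- **No rule codes a cut perineum as Intact.** This is true. A reader might infer that the plan makes episiotomies count as Intact and so turns a benefit of spontaneous pushing into harm. The document does not support that. It lists five labels without a rule, and no tear and no cut is a natural meaning of an intact perineum. Under that meaning nothing reverses.
- **The CRF may hold the rule.** It may, and an article may leave field definitions to it. But Table 5 does print the levels, and those levels do not settle this case and include a repair technique.
- **Spontaneous pushing is not shown to lower the episiotomy rate.** The Background cites fewer extended episiotomies, which concerns extension and not how often women are cut. The gap used above is an assumption.
- **There is no level for no episiotomy.** A reader might count this as a further error. It is not one, because a rate over a cohort implies its complement.
- **The outcome is not ranked as important.** Laceration is one of several unranked secondary outcomes with no success threshold. The episiotomy rate would be reported beside it, so an attentive reader could see what lies behind an odd Intact count. That helps only if the episiotomy rate is itself clean, and the suture level puts that in doubt.

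**Conclusion.** The point holds as a flaw in how two secondary outcomes are defined. The laceration comparison depends on a coding choice that Table 5 leaves open. The choice moves the difference in percent Intact by the between-cohort gap in episiotomy, and under the Intact coding the sign could change. How much this matters cannot be read from the protocol, which gives no episiotomy or tear rates. A 25-point gap gave −15 vs +10 points, a 10-point gap gave differences within noise, and a 5-point gap had little effect. The calculations assume that all 105 women per cohort contribute and that episiotomies are unextended.

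The misplaced suture level, and the mean or median assigned to a categorical item, are faults on the text alone and need no assumption. Nothing here touches the feasibility and acceptability criteria or the 105 per group. The matter is worth correcting before analysis, but it does not threaten the study's primary purpose.

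**What to change.** In Table 5 and the analysis coding:

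1. Define Intact as no tear and no episiotomy.
2. Report one mutually exclusive perineal variable for every woman: intact; spontaneous tear of degree I, II, III or IV; episiotomy without extension to degree III or IV; episiotomy with extension to degree III; episiotomy with extension to degree IV. Keeping III and IV apart retains the detail of the present scale.
3. Report episiotomy as none, mediolateral or midline, with n (%) in place of a mean or median.
4. Move intradermal suture to a separate repair-technique item, outside the episiotomy rate.
5. Apply the same written coding rule to both cohorts.

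The cost is recoding. Data collection ran from May to October 2023, so records already collected must be revisited for whether a cut was made, its type and the degree of any tear. This should need only the CRFs and the notes already reviewed, if those record the three facts; the CRF is not shown, so that is an assumption. No new participants or procedures are needed. The article planned to complete analysis by May 2024, after its publication in March 2024, so on that timetable the rule could still be set before results were final.
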